### Statistical analyses

The de-identified outcome data will be analyzed by a statistician blinded to group allocations using the Statistical Package for the Social Sciences V.19.0 statistical software package (SPSS, Chicago, IL, USA). Significant levels will be set at a *P* value of less than 0.05. Data analysis of baseline characteristics and of primary and secondary outcomes will be based on the intention-to-treat principle. The chi-squared test will be conducted for proportions and independent samples. The *t* tests will be analyzed for testing the baseline differences between the two groups. A repeated-measures analysis of variance (ANOVA) will be used to compare the effect of the treatments between the two study groups. Any missing data will be replaced according to the principle of the last observation and carried forward.

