**Methods/Design:**

In this randomized controlled clinical trial, we will enroll 124 participants with ISSNHL diagnosed 2 to 4 weeks prior to enrollment, who have shown little hearing improvement after routine Western medical treatment (i.e., corticosteroids). 62 of these participants will have flat audiogram and the other 62 will have a high-frequency drop audiogram; they will all take Methycobal while half of the flat type and half of the high-frequency drop type will also receive acupuncture treatments for 4 weeks in a four-group design. The primary outcome measure will be the effective rate of hearing improvement (defined as the proportion of patients with at least 15-dB improvement in the hearing loss frequency band). The secondary outcome will measure the improvements in Pure Tone Average, Word Recognition Score, and Tinnitus Handicap Inventory. The assessments of the participants will be made at baseline, after treatment (week 4), and at follow-up (week 28).

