### Randomization

Randomization will be accomplished by using SAS 9.1 software (SAS Institute Inc., Cary, NC, USA) and will be carried out by the Research Center of Clinical Epidemiology Affiliated with Peking University Third Hospital. For each of the two ISSNHL types, random allocation sequences will be generated, and opaque sealed envelopes will be created by computer. For both types, the ratio of patients in the treatment group and control group will be 1:1. The envelopes will be attached to one another in numerical sequence, and each envelope will be opened in sequence when a new patient is registered in the trial.

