### Sample size

Sample size was calculated on the basis of a single-arm pilot study that showed an effective rate of hearing improvement in 33% of the acupuncture-plus-Methycobal group according to the Chinese sudden hearing loss multi-center clinical study group [19]. We assumed that the effective rate of hearing improvement in the group with only Methycobal was 5%. The difference of the effective rate between the two groups was 28%. This study will be based on 0.8 power to detect a significant difference (α = 0.05, two-sided). In this case, it means that 26 participants will be required for each group, as calculated using PASS 2008. To allow for a 15% withdrawal rate, we plan to enroll 31 participants per group, amounting to a total of 124 participants.

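### Patients are randomised and sized within each audiogram type, but the analysis never says whether the primary conclusion is one overall comparison or one per type, so the 0.8 power and the 5% level belong to no defined test

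*Protocol article*

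**What the plan says.** **Design.** The Abstract (Methods/Design) plans 62 patients of each audiogram type, and "half of the high-frequency drop type will also receive acupuncture treatments for 4 weeks in a four-group design". The Randomization section adds: "For each of the two ISSNHL types, random allocation sequences will be generated", at 1:1 within each type.

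**Sample size.** The section takes from a single-arm pilot an "effective rate of hearing improvement in 33% of the acupuncture-plus-Methycobal group", assumes 5% on Methycobal alone, and uses power 0.8 with a two-sided level of 0.05. From this, "it means that 26 participants will be required for each group". With 15% withdrawal that becomes 31 per group, and the total of 124 is reached as four groups of 31.

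**Analysis.** Statistical analyses sets significance at P below 0.05. On testing proportions it says "The chi-squared test will be conducted for proportions and independent samples". Baseline t tests are for differences between two groups, and a repeated-measures ANOVA will "compare the effect of the treatments between the two study groups". The section does not mention audiogram type.

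**Objective.** It concerns patients with flat or high-frequency-drop audiograms, without saying whether one conclusion or two will be drawn.

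**The concern.** Design and sample size have four groups; the analysis language has two. The sample size arithmetic gives 0.8 power to a comparison inside one audiogram type. Nothing in the analysis section says that this is the comparison to be made, or how the 5% level applies if it is made twice.

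The Discussion in the Abstract says that positive results could lead to acupuncture being recommended as salvage therapy. What counts as positive should therefore be settled beforehand. As written, the overall result, the flat-type result or the high-frequency result could each be put forward as the primary finding. The Background also says that prognosis is closely tied to audiogram type, and the trial randomises on it, so leaving it out of the analysis needs a reason.

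**Working it through.** **Inputs (Sample size, Randomization, Abstract).** Response 33% against 5%; two-sided 0.05; 26 evaluable and 31 enrolled per cell; two types by two treatments. The protocol gives no rates by type, so the same rates are used in both types unless stated.

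**Step 1: reproduce the plan's figure.** With n per group, reject when |x₁ − x₂|/n ÷ √(2p̄(1 − p̄)/n) > 1.96, where p̄ = (x₁ + x₂)/(2n). Sum the product of the two binomial probabilities over the rejection region.

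- n = 25: power 0.783
- n = 26: power 0.802

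So 26 is the smallest size that reaches 0.80. Then 26/(1 − 0.15) = 30.6, rounded up to 31, and 31 × 4 = 124. The arithmetic is right, and it shows that 0.8 is the power of one comparison within one type.

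**Step 2: reading A, one pooled test (52 against 52).**

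- Power at 33% against 5%: 0.976 by the same enumeration.
- Type I error for common null rates of 5% to 30%: 0.044 to 0.051.
- Cochran-Mantel-Haenszel test stratified by type, simulated: power 0.976, so stratifying gains nothing at the planning rates.
- If the types differ in prognosis (assumed null rates 2% and 30%): error 0.033 unstratified, 0.048 stratified. Ignoring type makes the test conservative, not invalid.

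**Step 3: reading B, two per-type tests at 0.05 (26 against 26 in each).**

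- Power for both: 0.802² = 0.643.
- Power for at least one: 1 − (1 − 0.802)² = 0.961.
- Exactly one significant although the effect is the same in both: 2 × 0.802 × 0.198 = 0.318.
- Nominal error if either counts: 1 − 0.95² = 0.0975.

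Exact error for either, with e the exact per-type error:

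| Common null rate | e | 1 − (1 − e)² |
|---|---|---|
| 5% | 0.0215 | 0.043 |
| 10% | 0.0502 | 0.098 |
| 15% | 0.0555 | 0.108 |
| 20% | 0.0560 | 0.109 |
| 30% | 0.0552 | 0.107 |

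**Step 4: what each choice buys.**

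- If the control rate is 10% instead of 5% (assumption), a single-type test has power 0.56 and the stratified overall test 0.84.
- If only one type responds (33% against 5% in one, 5% against 5% in the other; assumption), the stratified overall test has power 0.65, below the 0.80 of the test within the responding type.
- Two per-type tests at 0.025 each have power 0.70 at 26 per cell. Reaching 0.80 needs 33 per cell by exact enumeration; 33/0.85 = 38.8, so 39 enrolled per cell and 156 in total. A pooled-variance normal approximation gives 36 per cell, hence 43 enrolled and 172 in total.

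**The case against.** The strongest reply is that the document has a consistent reading. The Randomization section speaks of a treatment and a control group for each type, and the sample size is one two-group comparison multiplied out to four cells. On that reading the two groups are the arms within a type, and the test, the 26 per group and the 0.8 all agree. Two prespecified populations, each reported at 0.05, is a defensible choice. This stands as a possible reading, but the text does not state it.

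Four stronger conclusions are tempting and are not supported:

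- **That the protocol commits to an unstratified pooled test.** The chi-squared sentence names no groups and no pooling. The phrase about two study groups belongs to the ANOVA sentence.
- **That the trial has about twice its nominal error.** This needs a rule that success in either type suffices, which the protocol never states. At its own 5% control rate the exact figure is 4.3%.
- **That both faults occur together.** Excess error arises only with two tests, and the power mismatch only with one pooled test.
- **That omitting the stratum costs substantial power.** At the planning rates the two tests are equal. A clear gap, such as 46% against 55%, needs an assumed extreme (15% against 2% in one type, 60% against 40% in the other). The Background describes both types as having a poor prognosis.

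Interval methods and interaction tests can properly be left to an analysis plan. The point here is narrower: the power and the level that the article does state are attached to no identified comparison.

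**Conclusion.** The point holds as an ambiguity with consequences, not as an error in the test or in the sample size. The figure of 26 per cell reproduces exactly as within-type power. The analysis section does not say whether that within-type comparison is the primary one.

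Under one pooled test the stated 0.8 understates the power (0.976), and the randomisation factor is unused. Under two tests with either sufficing, error can reach about 10% when null response is 10% or more, and the chance of succeeding in both types is 64%. These figures assume 33% against 5% in both types, 26 evaluable per cell and an uncorrected chi-squared test.

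It should be corrected, but it ranks below the changes without which the trial could not be interpreted.

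**What to change.** In Statistical analyses, name one primary comparison: response on acupuncture plus Methycobal against Methycobal alone, by a Cochran-Mantel-Haenszel test stratified by audiogram type, two-sided 0.05. Report each type's rates with confidence intervals as supporting results. Allow a type-specific claim only after the overall test is significant.

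In Sample size, state that 80% is the power within one type and that overall power is about 97% (0.976 with 52 per arm) if the same rates hold in both types.

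If the sponsor prefers two type-specific conclusions, say so, give a multiplicity rule and restate the power. With 0.025 per type, this means either 0.70 per type at the present size or 156 to 172 patients.

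The recommended change costs wording only, with no extra patients or data. Its downside is that type-specific claims depend on the overall test, which has power of about 0.65 if only one type responds.

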The treatment and prognosis of ISSNHL are closely related to the patient’s audiogram type [17]. According to the German guidelines, ISSNHL has six types [18]: (1) hearing loss at low frequencies, in the range of 250–500 Hz, which has the best prognosis; (2) hearing loss at middle frequencies, around 1000 Hz; (3) hearing loss at high frequencies, above 4000 Hz, which has a poor prognosis; (4) flat type, hearing loss at all frequencies, which also has a poor prognosis; (5) complete/profound deafness, extreme hearing loss at every frequency, which has the worst prognosis; and (6) others unspecified. A multi-center randomized controlled trial (RCT) for a pharmacological treatment in China [19] obtained type-differentiated prognosis data similar to those described in the German guidelines. Some studies showed that ISSNHL with low-frequency drop audiograms has the best prognosis and responds well to treatments [18, 20, 21], complete/profound deafness is difficult to treat [18], and patients with middle-frequency drop audiograms are rare [18]; therefore, ISSNHL patients with flat or high-frequency drop audiograms are more suitable for research than other types. Acupuncture therapy is a significant component of traditional Chinese medicine (TCM). In TCM theory, it is believed that ISSNHL is caused by the Yin-Yang imbalance of internal organs. Acupuncture is considered a useful treatment that brings about balance by stimulating acupoints to activate channels and improve and regulate the functions of Zang-Fu organs, Qi, and Blood according to *Huang Di Nei Jing* (a famous work of ancient TCM literature). Since ancient times in China, there have been reports of acupuncture being used to treat ISSNHL symptoms [22]. Recent studies have suggested that acupuncture may have beneficial effects on ISSNHL [23, 24], but evidence of acupuncture studies that have employed audiograms is limited. Furthermore, prior acupuncture studies did not account for the amount of time elapsed since ISSNHL onset, which is an important prognosis factor that may influence treatment outcomes. Therefore, this randomized controlled clinical trial was designed to evaluate the efficacy and long-term effects of acupuncture as a salvage therapy for patients who have not recovered 2 to 4 weeks after the onset of ISSNHL.

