### Participants

#### Inclusion criteria

Ages between 18 and 70;Diagnosis of ISSNHL [1, 25], defined as sudden hearing loss (≥30 dB) in less than 72 h affecting three consecutive frequencies;ISSNHL patients with flat or high-frequency drop audiograms according to pure tone audiometry;ISSNHL began 2 to 4 weeks prior;Hearing improvement of less than 50% since ISSNHL began.

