### Outcome measures

Audiometry (pure tone hearing test), Word Recognition Score (WRS), and Tinnitus Handicap Inventory (THI) will be used to assess the participants before and after treatment (at weeks 4 and 28). The primary outcome measure will be the effectiveness of hearing improvement, defined as the proportion of patients with an improvement of at least 15 dB in their hearing loss frequency band [25]. For hearing improvement, complete recovery will be defined as hearing level equal to that of the unaffected ear or to hearing prior to ISSNHL [25]. Hearing gains of greater than 30 dB will be considered significant, gains of 15 to 30 dB will be considered effective, and gains of less than 15 dB will be considered ineffective [25]. The secondary outcome will measure the improvements in Pure Tone Average (PTA) (dB HL) [2], in WRS [2] and in THI [26].

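### The unadjusted chi-squared test of the primary response is valid but leaves precision unused: it adjusts for neither days since onset nor baseline hearing, and the planned baseline t tests do not make up for this

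*Protocol article*

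**What the plan says.** All references are to the protocol article.

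- **Outcome measures:** the primary outcome is binary, "defined as the proportion of patients with an improvement of at least 15 dB in their hearing loss frequency band". Audiometry is done before treatment and at weeks 4 and 28.
- **Statistical analyses:** the test that fits this outcome is given in one sentence, "The chi-squared test will be conducted for proportions and independent samples". No covariate is named. The repeated-measures ANOVA in the same section names none either, and it does not suit a yes/no response. For baseline data the section plans t tests, which "will be analyzed for testing the baseline differences between the two groups". It does not say what would follow from their result.
- **Background:** earlier work is criticised for neglecting "the amount of time elapsed since ISSNHL onset, which is an important prognosis factor that may influence treatment outcomes".
- **Inclusion criteria:** onset is restricted, "ISSNHL began 2 to 4 weeks prior".
- **Randomization:** sequences are separate for the two audiogram types, 1:1 within each. Neither days since onset nor hearing level is a stratification factor.

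**The concern.** Onset date and baseline audiogram are known for every patient before allocation. A predictor of response that is known at entry can sharpen the treatment comparison if it is put into the analysis in advance. The stated test uses neither variable in this way. Measuring the outcome as a gain from baseline is not adjustment, because the room for a 15 dB gain still depends on the starting level.

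The baseline t tests do not fill the gap. Under randomisation any baseline difference is due to chance, so the hypothesis tested is already known to be true. A non-significant result does not show that a prognostic factor is balanced, and a significant one leaves the treatment estimate unchanged.

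At stake is some power and some protection against chance imbalance in a trial with 31 patients per group in each audiogram type. If covariates were instead chosen after the data were seen, the adjusted result would carry little weight.

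**Working it through.** **Inputs from the Sample size section:** response 33% v 5%, two-sided alpha 0.05, power 0.80, 26 evaluable per group, 15% withdrawal, 31 enrolled per group, 124 in total.

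**1. The plan's own figure.** Exact binomial enumeration of the uncorrected chi-squared test at 33% v 5% gives power 0.783 at 25 per group and 0.802 at 26, so 26 reproduces. Then 26/0.85 = 30.6, rounded up to 31, and 4 × 31 = 124. At 31 per group the power is 0.857. The sample size is not at fault.

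**2. Validity of the stated test.** With no effect and a common rate of 19% (the mean of 33% and 5%), exact enumeration gives a false-positive rate of 0.050 at 31 per group and 0.056 at 26.

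**3. Chance imbalance within one type.** The SE of a standardised baseline difference is √(2/31) = 0.254.
- Above 0.25 SD: 32% of trials.
- Above 0.3 SD: z = 0.3/0.254 = 1.18, so 24%. In at least one of the two types: 1 − 0.762² = 42%.
- Above 0.5 SD: 5%. Here z = 0.5/0.254 = 1.97, so a baseline t test becomes significant only at about this size. Imbalances of 0.25 to 0.5 SD, about 32% − 5% = 27% of trials, pass as non-significant.

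**4. Power with adjustment.** The document gives no strength for either covariate, so a range is assumed: two independent covariates with the same odds ratio per SD. Responses were simulated from a logistic model with marginal rates held at 33% and 5%, 31 per group. Chi-squared was compared with a covariate-adjusted score test.

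| Odds ratio per SD | Chi-squared | Adjusted |
|---|---|---|
| 1.5 | 0.85 | 0.86 |
| 2.0 | 0.85 | 0.88 |
| 2.5 | 0.86 | 0.91 |

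The gain is about 1 to 5 points. In a separate simulation with one baseline score of no prognostic strength, power was 0.85 for both tests at 31 per group, and 0.79 v 0.78 at 26.

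**5. Size of the adjusted test.** Its overall null rejection was about 0.052 to 0.059, against about 0.05 for chi-squared, so part of the gain in step 4 is excess size.

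**6. Error given an imbalance.** Under no effect, among trials with one covariate out of balance by more than 0.3 SD, rejection was 5.5% unadjusted v 5.7% adjusted at odds ratio 1.5, 6.3% v 6.2% at 2.0 and 6.7% v 5.6% at 2.5. The Monte Carlo error is about 0.7 points in a run of 5,000 trials, so the contrast is small.

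**7. Information available to a model.** Expected responders per type at 31 per group: 31 × (0.33 + 0.05) = 11.8; at 26 per group, 9.9. The chance of no control responder in a type is 0.95³¹ = 20%, or 0.95²⁶ = 26%. Ordinary maximum likelihood for the treatment odds ratio fails when this happens.

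**The case against.** The strongest reply is that the protocol does deal with onset time, by restriction. The Background makes its criticism and then confines the trial to patients 2 to 4 weeks from onset; the Discussion repeats that reasoning. A reader might infer that the trial ignores the very factor it faults others for ignoring. The documents do not support that. What stands is narrower: the window still spans two weeks, and nothing is done about the variation inside it.

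Prognostic strength inside the window is also unproven. The document contrasts recovery before and after about 2 weeks; it does not say that day 15 differs from day 27. If onset were uniform over the window (an assumption), the SD would be 14/√12 = 4.0 days and 0.3 SD only 1.2 days. Baseline threshold is never called prognostic, and audiogram type, which is, already governs randomisation. This stands, and it is why the gain is given as a range that starts near zero.

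A reader might also infer that the unadjusted test is biased or has an inflated error rate. Steps 2 and 6 do not support that. Nor would adjustment show whether benefit varies with time since onset: a main-effect covariate accounts for prognosis, and effect variation would need an interaction term.

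Lastly, covariates are often left to an analysis plan, and an unadjusted test is legitimate. That makes this an improvement to a test the article states, not a complaint of missing detail. The scarcity of responders in step 7 is a real limit on the remedy.

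**Conclusion.** The point holds as a loss of precision. The stated primary test controls its error rate but leaves unused one variable that the document calls prognostic and another that is plausibly so. The baseline t tests add nothing.

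The size is about 1 to 5 points of power at 33% v 5% with 31 per group. This rests on assumed odds ratios of 1.5 to 2.5 per SD for two independent covariates. It would be near zero if they are weak, and it is somewhat overstated because the adjusted score test is slightly liberal. There is no material overall type I error problem to correct. The change is worth making because it is cheap and is credible only if fixed in advance.

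**What to change.** In the Statistical analyses section:

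1. Remove the baseline t tests and describe baseline by group only.
2. Prespecify a covariate-adjusted analysis of the 15 dB response, with days since onset and baseline threshold in the affected band as the only continuous covariates.
3. Fit it over both audiogram types with a type term, adding treatment by type if type-specific effects are to be reported. A separate model within each type would rest on about 12 responders.
4. Use penalised likelihood or another small-sample method.
5. Report a standardised risk difference with a 95% confidence interval, and give the unadjusted chi-squared result alongside.

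No new data or visits are needed. The cost is some model dependence with few responders, including about a 20% chance of no control responder in a type at a 5% rate. Fixing two covariates in advance and keeping the unadjusted result in view limits it. The sample size was worked out for the chi-squared test and need not change.

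### The repeated-measures ANOVA for PTA, WRS and THI leaves out baseline value and audiogram type and does not fix its treatment test; a baseline-adjusted model of weeks 4 and 28 is more efficient at no extra cost

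*Protocol article*

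**What the plan says.** The Statistical analyses section of the protocol article gives proportions a chi-squared test and then states: "A repeated-measures analysis of variance (ANOVA) will be used to compare the effect of the treatments between the two study groups". Baseline appears there only in *t* tests, of which it says: "tests will be analyzed for testing the baseline differences between the two groups". No covariate is named.

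Three other sections bear on the point:

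- **Outcome measures.** The primary outcome is the proportion of patients who gain at least 15 dB. The secondary outcomes are improvements in PTA, WRS and THI. Assessments are at baseline, week 4 and week 28.
- **Randomization.** Separate 1:1 sequences are generated for the flat and the high-frequency drop type.
- **Background.** Prognosis is tied closely to audiogram type. Time since onset is described as a variable "which is an important prognosis factor that may influence treatment outcomes", in a criticism of earlier acupuncture studies.

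**The concern.** Baseline hearing, speech and tinnitus scores are likely to predict the later scores, and every patient has them. The stated analysis does not use them as covariates. It also leaves out the factor by which randomisation is stratified, which the Background treats as prognostic.

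With three visits, the term *repeated-measures ANOVA* covers several tests of quite different sensitivity. In one of them, the group main effect over all three visits, the pre-treatment visit is averaged into the treatment effect although no effect can exist there. The baseline *t* tests do not help: under randomisation a baseline difference arises by chance, and testing it neither answers a useful question nor corrects the imbalance.

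At stake are the precision and the clarity of the PTA, WRS and THI results.

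**Working it through.** **1. What is not affected.** The sample size rests on the primary proportion: 33% against 5%, two-sided alpha 0.05, power 0.80. The plan says "26 participants will be required for each group, as calculated using PASS 2008". Exact binomial power of the uncorrected chi-squared test at 26 per group is 0.802, so the figure reproduces. With 15% withdrawal, 26 / 0.85 = 30.6, rounded up to 31, and 4 × 31 = 124, as stated. None of this depends on the ANOVA.

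**2. Inputs for the secondary outcomes.** The documents give no SD, effect size or correlation for PTA, WRS or THI. The following are assumptions:

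- SD 1 at each visit.
- The same correlation r between any two visits (compound symmetry).
- True difference 0 at baseline and d = 0.5 at both weeks 4 and 28.
- Two-sided alpha 0.05.
- n = 62 per arm, which pools the two audiogram types (2 × 31).

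**3. Noncentrality under each reading.** Here n/2 = 31 and d² = 0.25, so (n/2)d² = 7.75.

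- *Baseline as a level, group main effect.* The effect is (0 + d + d)/3 = 2d/3 and the variance of a three-visit mean is (1 + 2r)/3. Noncentrality is 31 × 0.1111 / 0.667 = 5.17 at r = 0.5 and 31 × 0.1111 / 0.8 = 4.31 at r = 0.7.
- *Baseline as a level, group-by-time (2 df).* (n/2)(2d²/3)/(1 − r) = 5.167 / 0.5 = 10.33 and 5.167 / 0.3 = 17.22.
- *Change scores at weeks 4 and 28, group main effect.* The variance of the mean change is (1 + r)/2 + 1 − 2r = 1.5(1 − r). Noncentrality is 7.75 / 0.75 = 10.33 and 7.75 / 0.45 = 17.22, on 1 df.
- *Post-treatment visits only, unadjusted.* The variance is (1 + r)/2. Noncentrality is 7.75 / 0.75 = 10.33 and 7.75 / 0.85 = 9.12.
- *ANCOVA on the mean of weeks 4 and 28.* The variance is (1 + r)/2 − r². Noncentrality is 7.75 / 0.50 = 15.50 and 7.75 / 0.36 = 21.53.

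**4. Power (noncentral t or F).**

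| Test | r = 0.5 | r = 0.7 |
|---|---|---|
| Group main effect, three visits | 0.62 | 0.54 |
| Group-by-time, 2 df | 0.82 | 0.97 |
| Change scores, weeks 4 and 28 | 0.89 | 0.985 |
| Post-treatment visits, unadjusted | 0.89 | 0.85 |
| ANCOVA, mean of weeks 4 and 28 | 0.97 | 0.996 |

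ANCOVA at week 4 alone has 0.89 and 0.97. The full gain therefore belongs to the average of the two visits, not to each visit separately.

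**5. Analysis within one audiogram type.** With 31 per arm, power at r = 0.5 / 0.7 is 0.35 / 0.30 for the main effect, 0.51 / 0.74 for the interaction, 0.61 / 0.82 for change scores and 0.78 / 0.90 for ANCOVA.

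**6. How the gain varies with r.** The patients needed relative to ANCOVA are 1.5/(1 − r) times for the three-visit main effect, that is 3.0 at r = 0.5 and 5.0 at r = 0.7. For change scores the ratio is 3/(1 + 2r): 1.5 at r = 0.5, 1.25 at r = 0.7 and 1.07 at r = 0.9. With 31 per arm and r = 0.9, the interaction test has 0.997 against 0.999 for ANCOVA, so almost nothing is left to gain.

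**The case against.** The strongest reply is that the damaging version is not written down. A reader might infer from the visit schedule that baseline is one of three outcome visits, that the effect is therefore shrunk to 2d/3, and that several times as many patients are needed. The documents do not support that as a statement of fact. The Statistical analyses section names neither the time levels nor the tested term. Outcome measures speaks of improvements and the Discussion of changes in these scores, which fits an analysis of change at weeks 4 and 28 with no dilution. Even with baseline as a level, group-by-time is the usual treatment test, and it is not diluted either. This part of the reply stands: the dilution and the large multiples are conditional.

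Three further points also stand, in whole or in part:

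- The primary hearing result is a responder rate under a chi-squared test. It would be wrong to infer that the trial's main hearing conclusion or its sample size is weakened.
- If the analysis is run separately by audiogram type, type is already handled and its absence as a term does not matter. The reference to two study groups suggests pooling but does not settle it.
- Eligibility restricts onset to 2 to 4 weeks before entry, so the design already deals with much of the onset-time criticism made of earlier studies. Adjustment for days since onset is a choice, not a need.

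It can also be said that a condensed article leaves model details to a fuller document. That covers silence about covariance structure or software options. It does not cover the method itself: the article names the ANOVA as the treatment comparison and gives baseline no role beyond *t* tests. A better method can be recommended against that choice.

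**Conclusion.** The point holds as one of efficiency and clarity for PTA, WRS and THI only. The plan names an analysis with no baseline covariate and no term for the randomisation stratum, and it leaves the treatment test open between terms whose power, under the assumptions above, runs from 0.62 to 0.89 at r = 0.5 and from 0.54 to 0.985 at r = 0.7. A baseline-adjusted comparison of the two post-treatment visits reaches 0.97 and 0.996, higher than every reading examined.

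The loss is large only if the three-visit group main effect is the test. Against the interaction or change scores it is moderate at r = 0.5 and becomes small as r rises. The true size cannot be fixed from the documents. It depends on the assumed effect, equal SDs and correlations, and pooling over types. No gain from adjusting for audiogram type is counted in these figures.

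**What to change.** In the Statistical analyses section, replace the ANOVA sentence for PTA, WRS and THI with a model of the week 4 and week 28 values that contains baseline value, audiogram type, visit, arm and arm-by-visit. Report the adjusted difference between arms with a 95% CI at each visit. State in advance whether the treatment test is the difference at a named visit or the average of both visits, since the highest power shown above applies to the average. If the types are to be analysed separately, say so and drop the type term. Days since onset may be added but is optional. Present baseline characteristics descriptively and remove the *t* tests of baseline differences.

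The cost is wording only. Baseline value and audiogram type are already recorded for every patient, the baseline covariate uses one degree of freedom, and no patients, visits or measurements are added. The primary chi-squared comparison and the sample size stay as they are.
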